## Abstract

**Background:**

Pelvic nodal recurrences are being increasingly diagnosed with the introduction of new molecular imaging techniques, like choline and PSMA PET-CT, in the restaging of recurrent prostate cancer (PCa). At this moment, there are no specific treatment recommendations for patients with limited nodal recurrences and different locoregional treatment approaches are currently being used, mostly by means of metastasis-directed therapies (MDT): salvage lymph node dissection (sLND) or stereotactic body radiotherapy (SBRT). Since the majority of patients treated with MDT relapse within 2 years in adjacent lymph node regions, with an estimated median time to progression of 12–18 months, combining MDT with whole pelvic radiotherapy (WPRT) may improve oncological outcomes in these patients. The aim of this prospective multicentre randomized controlled phase II trial is to assess the impact of the addition of WPRT to MDT and short-term androgen deprivation therapy (ADT) on metastasis-free survival (MFS) in the setting of oligorecurrent pelvic nodal recurrence.

**Methods & design:**

Patients diagnosed with PET-detected pelvic nodal oligorecurrence (≤5 nodes) following radical local treatment for PCa, will be randomized in a 1:1 ratio between arm A: MDT and 6 months of ADT, or arm B: WPRT added to MDT and 6 months of ADT. Patients will be stratified by type of PET-tracer (choline, FACBC or PSMA) and by type of MDT (sLND or SBRT). The primary endpoint is MFS and the secondary endpoints include clinical and biochemical progression-free survival (PFS), prostate cancer specific survival, quality of life (QoL), toxicity and time to castration-resistant prostate cancer (CRPC) and to palliative ADT. Estimated study completion: December 31, 2023.

**Discussion:**

This is the first prospective multicentre randomized phase II trial assessing the potential of combined WPRT and MDT as compared to MDT alone on MFS for patients with nodal oligorecurrent PCa.

**Trial registration:**

ClinicalTrials.gov Identifier: NCT03569241, registered June 14, 2018, ;

Identifier on Swiss National Clinical Trials Portal (SNCTP): SNCTP000002947, registered June 14, 2018.

## Background

A proportion of prostate cancer (PCa) patients develop a local, regional (N1) or distant (M1) relapse following curative local treatment. For both local and distant relapse, different treatment recommendations are made in the EAU-EANM-ESTRO-ESUR-SIOG guidelines on Prostate Cancer [1]. The entity of regional nodal recurrence is not specifically mentioned in the guidelines although it is an emerging clinical situation with the introduction of new molecular imaging techniques like choline and more recently PSMA PET-CT in the restaging of recurrent PCa [2]. More specifically, a subgroup of these patients is being diagnosed with a recurrence confined to the regional lymph nodes and limited in number (oligorecurrence) using metabolic imaging [3, 4]. As there are no specific treatment recommendations for limited metastatic disease, different treatment approaches are currently used, mostly focusing on local ablative treatment using radiotherapy or surgery [5–8]. These treatments are coined metastasis-directed therapy (MDT) [5]. MDT, whether or not in combination with temporary androgen deprivation therapy (ADT), has the potential to reduce the subsequent risk of progression or even to cure limited regional nodal recurrence [5], and hereby postponing or even pre-empting the need for lifelong palliative ADT and its associated toxicity [9].

A recent systematic review showed that most published series on MDT are small with heterogeneous patient populations, making it difficult to make treatment recommendations [5, 7, 8]. To address these shortcomings, an international patient database on oligometastatic PCa recurrence (≤3 lesions) was established allowing to study a homogeneous patient population treated with stereotactic body radiotherapy (SBRT) [10]. A first analysis of this series showed that the majority of patients treated with SBRT for nodal recurrence, relapse within 2 years in nearby lymph node regions, with an estimated median time to progression of 12–18 months [11–13]. Similar results in terms of time to progression were observed in a large multi-institutional study exploring the role of salvage lymph node dissection (sLND) after nodal recurrence [14]. These comparable results could probably be explained by a lack of sufficient sensitivity of the current imaging techniques to perform a lesion-based approach, either by SBRT or sLND. An elective nodal irradiation approach using whole pelvic radiotherapy (WPRT) in addition to MDT could delay or even prevent such relapse [12, 15–17]. Improved progression-free survival (PFS) rates have been observed with WPRT in radiotherapy series [15–17], as well as after sLND as demonstrated in the retrospective study by Rischke et al. [12].

The current trial wants to explore the potential benefit in terms of metastasis-free survival (MFS) of an elective nodal approach by adding WPRT to either sLND or as alternative to focal SBRT. The proposed trial randomizes patients with oligorecurrent nodal PCa following primary PCa treatment to either MDT (sLND or SBRT) or WPRT plus MDT (focal radiotherapy boost or sLND). As two recent trials have suggested a progression-free and even overall survival benefit by adding temporary ADT to local therapy in case of biochemical recurrence [18, 19], a positive effect could also be expected for regional recurrence. Although the optimal duration of ADT is unknown, a minimal duration of 6 months of ADT seems advisable in this setting and is mandatory for both arms.

This trial will improve our insights in the pattern of recurrence following these treatment modalities with the expectation that WPRT will reduce the number of nodal relapses, improving MFS and postponing the need for palliative systemic treatment while maintaining quality of life (QoL).

## Methods & design

This study is approved by the Ethics committee of the Ghent University Hospital (EC/2018/0130) and is registered on both ClinicalTrials.gov (NCT03569241) and Swiss National Clinical Trials Portal (SNCTP000002947). This is a prospective multicentre randomized phase II trial designed for patients with PET-detected pelvic nodal oligorecurrence (≤5 nodes) following radical local prostate treatment (radical prostatectomy [RP], primary radiotherapy [RT] or both). In the standard arm A, patients will receive MDT by means of SBRT or sLND, combined with short-term ADT (6 months). In the experimental arm B, WPRT will be added to MDT (focal radiotherapy boost or sLND) and short-term ADT (6 months). It will be emphasized that the participation is voluntary and that the patient is allowed to refuse further participation in the protocol whenever he wants, which will not prejudice the patient’s subsequent care. Estimated study completion: December 31, 2023.

### Objectives

#### Primary endpoint

MFS: time between randomization and the appearance of a metastatic recurrence (any M1) as suggested by choline, FACBC or PSMA PET-CT/PET-MRI or death due to any cause. In case of biochemical progression, restaging will be performed, preferably with the same PET-tracer. In case of negative PET findings at biochemical relapse, repeated PET imaging should be performed on a 6-monthly basis or earlier if clinically indicated.

#### Secondary endpoints

Clinical PFS: time between randomization and the appearance of a new recurrence (any N1 or M1) as suggested by PET-CT or PET-MRI, symptoms related to progressive PCa or death due to any cause.Local recurrence: evidence of a recurrence on imaging inside the surgical or radiotherapy field. Confirmation per biopsy is recommended. For radiotherapy schedules, local response and local progression is defined as per RECIST 1.1 criteria.Regional nodal recurrence: radiographic evidence (PET-CT or -MRI) of lymphadenopathy in the pelvis, outside the surgical or radiotherapy field. Histologic confirmation is recommended, especially in the absence of biochemical recurrence.Distant recurrence: appearance of distant metastases (M1a, M1b, M1c) outside the pelvis evidenced by PET-CT or -MRI.Biochemical PFS: time between randomization and the day of the first recorded biochemical progression (as defined below), clinical progression or death due to clinical progression.RP at diagnosis: biochemical recurrence = PSA > 0.20 ng/mL, confirmed 2 weeks later.Prostate radiotherapy at diagnosis: biochemical recurrence = PSA nadir + 2 ng/mL (Phoenix definition).Patients whose PSA does not drop below 0.20 ng/mL (if previous RP) or below the level before treatment (if previous prostate radiotherapy) at time of first response assessment at 3 months follow-up, are considered as non-responders to treatment and are considered to have a biochemical recurrence in case a second measurement at least 2 weeks later confirms a stable or rising PSA above this level.Time to start of hormonal treatment: time from trial randomization to start of hormonal treatment.Time to castration-resistant disease: time from trial randomization until castration resistant status as defined in the EAU-guidelines [1].PCa-specific survival: time from trial randomization until death due to PCa.Overall survival (OS): time from trial randomization until death from any cause.Acute and late toxicity due to radiotherapy will be assessed according to the National Cancer Institute Common Terminology Criteria for Adverse Events (CTCAE) version 4.0 [20], with special attention for rectal, gastro-intestinal and urinary adverse events. Surgery related morbidity, e.g. intra-operative complications (blood loss, injury to other pelvic organs …), and post-operative surgical complications will be scored using the Clavien-Dindo Classification of Surgical Complications [21].Acute toxicity: occurring during and up to 3 months after treatment completion.Late toxicity: occurring later than 3 months after treatment completion.Quality of life (QoL) scoring using the EORTC QLQ-C30 supplemented with QLQ-PR25. Raw scores will be transformed to a linear scale ranging from 0 to 100 according to the EORTC manual. The multi-item scales of the QLQ PR-25 will be analysed at both the individual item and the scale level. The results will be presented in accordance with recent guidelines for reporting health related QoL randomized controlled trials [22].Pattern of progression.Sensitivity/specificity of PET-imaging for the detection of nodal recurrences: limited to patients undergoing surgery.Biomarker discovery: to develop a miRNA panel predictive for treatment response using whole genome miRNA expression profiling [23].

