The gross target volume (GTV) will be defined as all known gross disease before any treatment, defined by CT/MRI/PET-CT images and/or clinical information. A GTV_PB may be defined with the help of MRI and PET imaging.The CTV will encompass regions at risk of microscopic extension. For CTV_PB, consensus guidelines such as EORTC, RTOG or FROGG are being followed [29–31]. The CTV_LNN consists of the pelvic lymph node regions as described in the RTOG guidelines [31], with the exception that delineation of the common iliac lymph nodes should start at the L4/L5 interspace [32] and should encompass the GTVs. No CTV is mandatory for SBRT.The PTV (PTV_PB, PTV_SBRT and PTV_LNN) will provide margin around the CTV to compensate for variability in daily treatment set-up and internal CTV motion due to breathing or motion during treatment. PTV_PB is created by a 5 to 10 mm margin for centres with or without image-guided radiotherapy, respectively. The PTV_LNN must include the entire CTV_LNN plus a minimum 3D-margin of 5 mm. For the nodal GTVs located within CTV_LNN, a margin of 5 mm is used. The PTV_SBRT should encompass the GTV with a minimal margin of 3 mm in all directions.
4.Dose prescription:Intensity modulated radiotherapy (IMRT) or use of rotational techniques is mandatory in case of WPRT and SBRT. In case of SBRT, treatment with Cyberknife® is allowed. 3D conformal technique is not allowed in this trial.
WPRT or PB-RT:All fields and the entire PTV_LNN must be treated daily for 5 days per week in a once-daily schedule of 1.8 Gy per fraction, for a total dose of 45 Gy in 25 fractions. The GTV should receive an integrated boost to a median dose of 65 Gy in 25 fractions, 2.6 Gy per fraction. If a suspicious node is still present following sLND, it is allowed to boost the GTV to the same dose during WPRT. In case of PB-RT, the PTV_PB should receive at least 66 Gy in 33 fractions.

Normalization of the treatment plan will cover 95% of the PTV_LNN or PTV_PB with the prescription dose. Furthermore, 98% of the PTV_LNN or PTV_PB should receive 95% of the prescription dose with 2% of the PTV not exceeding 107% of the prescribed dose.

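### Local and regional nodal recurrence are separated by the treated field, which differs by arm, so counts of regional relapse are not comparable between arms

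*Protocol article*

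**What the plan says.** The Secondary endpoints section places three recurrence classes directly beneath clinical PFS. The first is "Local recurrence: evidence of a recurrence on imaging inside the surgical or radiotherapy field". For this class it adds: "For radiotherapy schedules, local response and local progression is defined as per RECIST 1.1 criteria". The second is "Regional nodal recurrence: radiographic evidence (PET-CT or -MRI) of lymphadenopathy in the pelvis, outside the surgical or radiotherapy field". The third, distant recurrence, is defined by anatomy as disease outside the pelvis.

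The clinical PFS event itself is worded more broadly: "Clinical PFS: time between randomization and the appearance of a new recurrence (any N1 or M1) as suggested by PET-CT or PET-MRI", or symptoms of progression, or death. Local recurrence is not named as an event. Pattern of progression is a secondary endpoint of its own.

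The Radiotherapy section sets the fields. For focal treatment, "The PTV_SBRT should encompass the GTV with a minimal margin of 3 mm in all directions". For WPRT, "The CTV_LNN consists of the pelvic lymph node regions as described in the RTOG guidelines", with the common iliac nodes starting at the L4/L5 interspace and the known gross disease included. The Background states the expectation that "WPRT will reduce the number of nodal relapses".

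**The concern.** A between-arm comparison needs an outcome that means the same thing in both arms. Here the line between local and regional is the edge of the treated volume, and enlarging that volume is the experimental intervention. A new pelvic node with the same position, appearance and timing can therefore carry a different label depending on the allocated arm. The wording on evidence also differs: regional recurrence rests on PET, whereas RECIST 1.1 is cited for local progression after radiotherapy.

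Fewer nodal relapses is what the protocol expects WPRT to achieve. If nodal relapse is tabulated by these classes, part of that result can come from labelling alone. The trial is meant to inform a decision about phase III, and pelvic control is the mechanism it proposes, so readers will give that table weight.

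**Working it through.** **1. The plan's own figure, and whether this point touches it.** Inputs from Sample size: medians 24 and 36 months, two-sided alpha 0.20, power 80%, accrual 48 months, further follow-up 24 months, loss 5%.

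- HR = 24/36 = 0.667. Schoenfeld events = 4(1.2816 + 0.8416)²/(ln 0.667)² = 110. Freedman's formula gives 113.
- Event probability per arm = 1 − [exp(−24λ) − exp(−72λ)]/(48λ), with λ = ln 2/median. This gives 0.729 (A) and 0.589 (B), mean 0.659.
- Schoenfeld: 110/0.659 = 167, and 167/0.95 gives 176. Freedman: 113/0.659 = 171, and 171/0.95 gives 181. The stated 178 lies between them. Power at 178 with 5% loss is 80.5%.

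The primary endpoint counts M1 disease or death and does not use the local/regional split, so neither MFS nor 178 changes.

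**2. The same new pelvic node, away from the index node, under each treatment.**

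| MDT stratum | Arm A field | Arm B field | Label in A | Label in B |
|---|---|---|---|---|
| SBRT | node plus at least 3 mm | pelvic nodal regions | regional | local if inside the WPRT field |
| sLND, node inside template | template | template plus WPRT | local | local |
| sLND, node outside template | template | template plus WPRT | regional | local if inside the WPRT field |

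Within each stratum the arm B field contains the arm A target and adds to it. With identical disease, labelling can only move nodes from regional to local in arm B, never the other way.

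**3. How large the shift could be.** The document gives no field coverage, so this is an illustration under assumptions, with no true treatment effect. Let p be the risk of pelvic nodal relapse in both arms, r the share of relapse sites inside the arm A field, and q the share inside the arm B field.

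- Regional recurrence: A = p(1 − r), B = p(1 − q).
- Apparent HR = ln(1 − B)/ln(1 − A).
- p = 0.60 is assumed. The Discussion says that more than 60% of patients relapse in adjacent node regions after SBRT or sLND, without giving an arm-specific risk.
- r = 0.05 is assumed for SBRT. r = 0.50 is used for sLND, from the Discussion's statement that extended sLND covers about half of the landing sites.
- q = 0.50, 0.80 and 0.95 are assumed.

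| q | Regional in B | HR if r = 0.05 (A = 57%) | HR if r = 0.50 (A = 30%) |
|---|---|---|---|
| 0.50 | 30% | 0.42 | 1.0 |
| 0.80 | 12% | 0.15 | 0.36 |
| 0.95 | 3% | 0.04 | 0.09 |

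For example, q = 0.80 and r = 0.05 give ln(0.88)/ln(0.43) = 0.15. With p = 0.40 the ratios barely move (0.47, 0.17 and 0.04 for r = 0.05).

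The missing regional relapses reappear as local ones. At q = 0.80 and r = 0.05, local recurrence reads 0.60 × 0.80 = 48% in B against 0.60 × 0.05 = 3% in A. The total is 60% in both.

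**4. Clinical PFS.** Two readings are open. If N1 is anatomical, as in the Background, where it labels regional relapse without mention of a field, an in-field pelvic node in arm B is an event on PET exactly as in arm A. If N1 means the regional class defined just below, that node is local, and the text does not say whether or by which criterion it counts.

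**The case against.** The strongest reply is that clinical PFS is not biased as written. It counts any N1 or M1 on PET, without qualification, in both arms. This is a fair plain reading and it stands. A reader might infer from the sub-definitions that clinical PFS is built to favour arm B. The document does not support that as a fact, because it depends on which reading is applied. What remains is that the sub-definitions sit directly under clinical PFS and the text does not settle the choice.

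A reader might also infer that RECIST makes arm B relapses harder to call or later. That is not shown. The sentence covers all radiotherapy, so in-field relapse after arm A SBRT falls under it too. It pairs progression with response, which suggests treated lesions rather than new nodes in electively irradiated tissue. The protocol does not set out the RECIST criteria.

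Third, Data analysis plans comparisons of MFS, PFS and OS, and none of regional recurrence alone. The hazard ratios above therefore measure a labelling effect and do not predict a planned test. Relapses are relabelled rather than lost, and arm B's local rate would look worse. This limits the harm, but pattern of progression remains a stated endpoint.

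Finally, in-field versus out-of-field relapse is informative in a trial about elective field size. That is a reason to keep it as a descriptor, not to let it define the class compared between arms.

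**Conclusion.** The point holds for regional nodal recurrence and for pattern of progression reported by the stated classes. Both will tend to show fewer regional nodal relapses in arm B with no true effect. The direction follows from the definitions and the fields. The size does not: the range of 0.04 to 1.0 rests on assumed relapse risk and coverage, and the shift vanishes where the WPRT field adds no relapse sites to the arm A field. It is largest in the SBRT stratum and smaller with sLND.

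It would go too far to say that regional relapse is close to impossible in arm B, since that needs a coverage figure the document does not give. For clinical PFS the finding is an ambiguity, not a demonstrated bias. MFS and the sample size are unaffected. Severity: should-fix, on secondary endpoints.

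**What to change.** For the between-arm comparison:

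- Define regional (N1) recurrence by anatomy and identically in both arms: any new PET-positive pelvic node below the aortic bifurcation, inside or outside a treated field. The inclusion criteria already use that upper limit.
- State that every such node is a clinical PFS event by the same PET criterion in both arms.
- Limit the RECIST 1.1 sentence to response and progression of the treated lesions.
- Keep in-field or out-of-field as a separate descriptive item, reported alongside the anatomical site.

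The cost is a change of wording and, at most, one additional case report form item. The Follow-up section already requires the location of progression to be recorded, so the anatomical class should be obtainable for patients already enrolled. The change should be made before any comparison by arm.

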
### Inclusion criteria

Histologically proven initial diagnosis of adenocarcinoma of the prostate.Biochemical relapse of PCa following radical local prostate treatment (RP, primary RT or RP +/− prostate bed [PB] adjuvant/salvage RT) according to the EAU guidelines 2019 [1].Following RP, patients with a biochemical relapse are eligible in case a nodal relapse is detected in the pelvis even in the absence of prior postoperative PB radiotherapy (adjuvant or salvage).In case of a suspected local recurrence following primary RT, a biopsy should confirm local recurrence. Patients with a confirmed local recurrence are eligible in case they also undergo a local salvage therapy.Nodal relapse in the pelvis on choline, PSMA or FACBC PET-CT or PET-MRI with a maximum of 5 positive nodal lymph nodes. The upper limit of the pelvis is defined as the aortic bifurcation.WHO performance state 0–1Age ≥ 18 yearsAbsence of any psychological, familial, sociological or geographical condition potentially hampering compliance with the study protocol and follow-up schedule; those conditions should be discussed with the patient before registration in the trial.Before patient registration/randomization, written informed consent must be given according to ICH/GCP and national/local regulations.

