### Pre-randomization and evaluation

Patients must be restaged within 8 weeks prior to randomization with either a whole-body choline, PSMA or FACBC PET-CT/−MRI to exclude M1 disease (para-aortic node(s), bone or visceral metastases). Additional imaging modalities to confirm or to rule out M1 disease are optional. For patients without prior RP it is recommended to perform a multiparametric MRI of the prostate to rule out local recurrence. Local relapses must be biopsy proven. The following pre-treatment work-up, which is also depicted in Table 1, must be performed:

**Table 1 Tab1:** Summary of study visits and procedures

TIMEPOINT				STUDY PERIOD						
	Screening		Allocation	Treatment period			Follow-up period			
	Within 8 weeks prior to randomization	Within 2 weeks prior to randomization	Baseline	Start	During	End	1 month after treatment ± 7 days	3 months after treatment ± 14 days	6 months after treatment ± 14 days	6-monthly, yearly, until progression (g) ± 14 days
Window										

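### Distant recurrence is limited to lesions outside the pelvis, so a pelvic bone metastasis is M1 but is labelled local or left unclassified, and the label depends on the arm

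*Protocol article*

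**What the plan says.** Under Primary endpoint, the MFS event is "the appearance of a metastatic recurrence (any M1) as suggested by choline, FACBC or PSMA PET-CT/PET-MRI or death due to any cause". No anatomical limit is attached to M1.

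Under Secondary endpoints, clinical PFS counts "the appearance of a new recurrence (any N1 or M1) as suggested by PET-CT or PET-MRI", together with symptomatic progression and death. Three recurrence categories follow:

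- Local: "Local recurrence: evidence of a recurrence on imaging inside the surgical or radiotherapy field". The wording names no tissue or organ.
- Regional nodal: imaging evidence of "lymphadenopathy in the pelvis, outside the surgical or radiotherapy field".
- Distant: "Distant recurrence: appearance of distant metastases (M1a, M1b, M1c) outside the pelvis evidenced by PET-CT or -MRI".

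Elsewhere, bone and viscera carry no pelvic limit. Pre-randomization and evaluation requires whole-body restaging "to exclude M1 disease (para-aortic node(s), bone or visceral metastases". The Exclusion criteria bar bone and visceral metastases without regard to site, and qualify only the nodal criterion by the aortic bifurcation. The Inclusion criteria set the boundary in the item on nodal relapse: "The upper limit of the pelvis is defined as the aortic bifurcation".

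Pattern of progression is a listed secondary endpoint. The Follow-up section asks that the location of progression be recorded, and the Background gives insight into the recurrence pattern as an aim of the trial.

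**The concern.** A pelvic boundary makes sense for lymph nodes, because it separates N1 from M1a. The distant-recurrence definition applies the same boundary to M1b and M1c by naming them alongside M1a. Bone within the pelvis then drops out of the distant category, although the same lesion would have made the patient ineligible as M1 at entry.

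Such a lesion cannot be regional, because that category needs lymphadenopathy. Whether it is local depends only on whether it lies in the treated field, and the extent of that field is what randomization changes. The breakdown of recurrences by site is a main means of showing whether WPRT alters where the disease returns, and it would rest on categories that sort the same lesion differently in the two arms.

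**Working it through.** **Step 1. Apply each rule to one case.** Take a new sacral metastasis on PET, below the aortic bifurcation and so inside the pelvis. Suppose it lies within the WPRT volume in an arm B patient. Suppose the same lesion arises in an arm A patient whose SBRT treated a node elsewhere in the pelvis.

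| Rule in the article | Arm B, lesion within WPRT volume | Arm A, lesion away from SBRT volume |
|---|---|---|
| MFS event (any M1) | yes | yes |
| Clinical PFS event (any N1 or M1) | yes | yes |
| Distant recurrence | no: inside the pelvis | no: inside the pelvis |
| Regional nodal recurrence | no: not a node | no: not a node |
| Local recurrence | yes: in field | no: out of field |
| Resulting label | local | none |

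The two survival endpoints treat the patients alike; the site categories do not.

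**Step 2. Compare the fields.** The Radiotherapy section sets the SBRT target as the gross nodal volume plus at least 3 mm. The WPRT target is the pelvic nodal regions, starting at the L4/L5 interspace for the common iliac nodes, plus at least 5 mm. The WPRT field is therefore much the larger, and a pelvic bone lesion is more likely to be in field in arm B. The contrast is one of degree: surgical fields occur in both arms, and prostate-bed radiotherapy is allowed in arm A. Nor does WPRT cover the whole bony pelvis, so some arm B lesions would also be unclassified.

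**Step 3. Check whether the design figure depends on the disputed definition.** The Sample size section gives 178 patients, median MFS 24 versus 36 months, two-sided alpha 0.20, 80% power, 48 months of accrual plus 24 of follow-up, and 5% loss.

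- Events (Schoenfeld): 4 × (1.2816 + 0.8416)² / (ln 1.5)² = 109.7, so 110.
- Event probability per arm, with λ = ln 2 / median: 1 − (e^(−24λ) − e^(−72λ)) / (48λ). This gives 0.729 for a median of 24 months and 0.589 for 36 months, mean 0.659.
- Patients: 110 / 0.659 = 167; 167 / 0.95 = 176 after rounding up.
- With Freedman's formula: 25 × (1.2816 + 0.8416)² = 112.7, so 113 events, and 113 / 0.659 / 0.95 gives 181.

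The stated 178 lies between the two. It is built on MFS events, which the Primary endpoint section defines without using the distant-recurrence category, so the labelling problem leaves it unchanged.

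**Step 4. Ask what would happen to MFS if sites did use the distant definition.** Suppose a share a of arm A events and a share b of arm B events were missed. The hazard ratio would be multiplied by roughly (1 − b) / (1 − a). If both arms lost the same share, say an assumed 15%, the factor is 0.85 / 0.85 = 1 and the ratio does not move, although events and power are lost. It moves only if a and b differ. The documents give neither share, nor the frequency of pelvic bone metastases.

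**The case against.** The strongest reply is that the primary endpoint does not use the distant-recurrence definition at all. It counts any M1, the restaging section lists bone under M1 without a site limit, and no in-field exception is made. A site that follows the endpoint as written counts the sacral lesion in either arm. That stands, and it confines the certain defect to the site breakdown.

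A reader might go further and infer that MFS is biased in favour of WPRT because arm B lesions are absorbed into the local category. The documents do not support this. A lesion that fails the distant definition fails it in arm A too, where it may have no category at all. If failing that definition loses the event, both arms lose events; if the any M1 rule rescues the unclassified arm A lesion, it equally rescues the arm B lesion labelled local. A shift towards WPRT follows only if arm B alone is assumed to lose events, and nothing in the text gives that.

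It can also be said that the words about the pelvis were loose shorthand for disease beyond the pelvic nodes, that a recorded anatomical site could be reclassified at analysis, and that the full protocol or case report form may be clearer. These are fair points and they limit the harm. But the article states a rule, nothing in it signals shorthand, and the rule conflicts with its own use of M1. This is a stated definition that is wrong, not a detail left to another document.

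**Conclusion.** The definitions conflict. Under the published wording, a pelvic bone metastasis is M1 for eligibility, MFS and clinical PFS, yet it is not distant: it is local in field and unclassified out of field. The same gap applies to visceral M1c disease within the pelvis. Because field size differs by arm, the local/regional/distant breakdown and the pattern of progression endpoint are open to an artefact related to treatment.

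The number of patients affected cannot be stated, because the documents give no share of recurrences in pelvic bone or viscera.

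MFS, clinical PFS and the sample size are unaffected provided any M1 is applied as written. A risk to MFS exists only if sites take the distant-recurrence wording as the test for M1. That is conceivable, since it is the only endpoint wording that spells out M1a to M1c, but its size and direction cannot be derived from the documents. The point deserves correction because the categories feed a stated aim of the trial and the allocation is open label, not because the primary result is shown to be at risk.

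**What to change.** Reword the recurrence definitions as follows:

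- **Distant recurrence:** any M1a, M1b or M1c lesion on PET, including bone and viscera within the pelvis, irrespective of the surgical or radiation field.
- **Boundary:** the aortic bifurcation separates pelvic from distant disease for lymph nodes only.
- **Local recurrence:** limited to nodal, prostate or prostate-bed disease within the treated field.
- **Link to the primary endpoint:** state that every M1 lesion is an MFS event and may not be coded as local.

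If any progressions have already been coded, recheck those recorded as local or left uncategorised against the recorded anatomical site. The cost is a few sentences in the endpoint section and a matching note in the case report form guide. No extra imaging or visits are needed, and the sample size does not change.
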